### **7.3 Adverse Experiences related to Central Venous Catheter**

#### **Arterial Puncture and Bleeding**

During the insertion of the CVC there is a potential for inadvertent arterial puncture. This occurs in 8.4% of radiologically placed catheters. Bleeding occurs in 0.4% of placements of tunneled catheters [131].

Hematomas and bleeding are generally treated conservatively with firm pressure. Most percutaneous arterial punctures pose few complications and most are often not reported [131].

#### **Deep Vein Thrombosis**

The mechanism of catheter thrombosis is poorly understood, but is thought to be related to vascular injury from the catheter. The incidence of symptomatic thrombosis of a tunneled catheter occurs at a rate of 0.06 per 1000 days use for homecare patients [122]. The risk of a symptomatic thrombosis developing is more likely to occur within the first week of placement of the catheter, and again after it has been in place for more than 30 days [122, 132]. Patients who have developed one catheter thrombosis are at greater risk of developing future thrombosis [135].

Upper extremity deep vein thrombosis often present with upper extremity, neck and facial edema. The extremity may be cool and a low-grade fever or tachycardia may be present. Half of all patients with deep vein thrombosis present with no symptoms. Ultrasonography is highly predictive of detecting distal deep vein thrombosis and is more reliable than V/Q scan or impedance plethysmography. Contrast venography may be diagnostic for more central lesions [106].

Central venous catheters should be removed in the event of deep vein thrombosis. The incidence of pulmonary embolus is increased if left in place, even when therapeutic anticoagulation is obtained [181].

### **Exit Site Infections**

Infections of the tunneled catheter exit site occurs 0.36 incidences per 1000 days of use in the homecare setting [122]. These infections may result in cellulitis, abscess or fasciitis.

Wound infections are generally diagnosed clinically, with the presentation of tenderness, warmth, induration, erythema, drainage and fever. Wound drainage should be cultured.

The study drug can be maintained and the central venous catheter kept in place if the subject develops a local exit site infection, unless otherwise determined by an infectious disease specialist.

Each site will be required to have an Infectious Disease specialist available as a consultant and for clinical consultation. Any subject who presents with clinical signs and symptoms of infection, either at exit site or intravascular infection, will be referred to an infectious disease specialist for clinical evaluation.

### **Functional Problems**

With prolonged use, or through accident, the catheter may crack, break, infiltrate or become partially or completely withdrawn. Using metal clamps, repeated clamping over the same site, using sharp objects around the catheter and failing to properly secure the catheter can lead to these problems.

The use of the study drug should be held until the issue of the catheter's integrity and sterility is resolved. If the catheter is removed, the study drug can be continued through a peripheral line or by intramuscular injection temporarily.

### **Intravascular Related Infections**

Systemic infections related to CVCs result from both tracking of bacteria along the tunneled aspect of the catheter and by contamination of the catheter hub [125-129]. Organisms that typically cause these infections are *Staphylococcus aureus*, *S. epidermidis*, streptococcus species, gram-negative bacilli and *Candida* spp. [127-129]. The incidence of catheter-related bloodstream infections was identified as 0.34 for every 1000 days of use in patients with catheters being cared for at home [122].

When a systemic bloodstream infection is present, patients may present a clinical picture of fever, rigors, hyperventilation, malaise and a general toxic appearance. A leukocytosis is often present and there may be pain or drainage at the catheter insertion site. A new heart murmur may be evident on physical exam. Multiple blood cultures obtained peripherally and centrally

via the catheter may confirm the diagnosis. Other sources of infection are ruled out through physical exam, chest x-ray, blood and urine laboratory data, including urine culture, and through imaging studies that are clinically indicated.

If a systemic infection is suspected, the study drug may be continued or discontinued as recommended by an infectious disease expert. Study drug can be given either through the central catheter or through a peripheral line. Antibiotics can be empirically initiated, but should not include another cephalosporin. Treatment should be guided by the organism or organisms identified in the blood cultures. The catheter should be removed when there is evidence that the subject is hemodynamically unstable or if *S. aureus* or a fungemia is present. The catheter may need to be removed if coagulase-negative staphylococcus or a gram-negative organism is identified, based on the clinical judgment of infectious disease consultant. Once the infection has resolved, the study drug may be resumed.

Any subject who presents with signs and symptoms of intravascular infection will be referred to an infectious disease specialist for clinical consultation.

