## **Candidiasis**

Candidiasis is associated with concurrent antibiotic use. This may present as mucocutaneous or rarely invasive disease (e.g. tissue dissemination, skin lesions, ocular disease, or osteomyelitis) [173]. Genital candidiasis occurs in less than 1% of patients treated with ceftriaxone [103]. Diagnosis of fungal infection involves visual inspection for diagnosis of thrush. If not entirely clear, microscopic examination of mouth scrapings or culture can be done. Genital candidiasis is diagnosed by KOH preparation or wet prep of vaginal secretions. Invasive candidiasis/sepsis involves more extensive monitoring of vital signs and serum white blood cell count. Complete blood count with differential, blood culture, blood pressure, temperature should all be evaluated [173].

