## **8. CRITERIA FOR INTERVENTION SUSPENSION, RECHALLENGE, OR PERMANENT DISCONTINUATION**

### **8.1 Intervention Suspension Related to Ceftriaxone Use**

**Study drug will be suspended under the following circumstances:**

(Please refer to the Manual of Operations for details regarding management of AEs)

- If the subject has *C. difficile* infection and is concurrently systemically ill with fever, leukocytosis or if the symptoms are refractory to treatment
- If the *C. difficile* infection results in pseudomembranous colitis
- If the subject is being treated for severe dehydration
- If the subject is symptomatic from biliary sludge
- If the subject is diagnosed with symptomatic cholelithiasis
- If the subject is diagnosed with invasive candidiasis
- If the subject is diagnosed with acute interstitial nephritis
- If the subject is diagnosed with acute tubular necrosis
- If the subject is diagnosed with renal failure
- If the serum creatinine doubles as compared to the screening visit value, the test will be repeated. If the value is confirmed (doubled as compared to screening visit value), study drug will be suspended while subject is evaluated.
- If the urinalysis is positive for Wright's or Hansel's stain as this is suggestive of eosinophiluria, or allergic interstitial nephritis
- If the spot urine protein is greater than 1000 mg. This is likely an indication of severe renal toxicity
- If the subject becomes oliguric, which is defined as urine output less than 500 mL/day. This can be an indication of severe renal toxicity
- If the Absolute Neutrophil Count (ANC) is less than 1.2 th/cmm

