**Subjects may be rechallenged with study drug under the following circumstances:**

- Upon resolution of pseudomembranous colitis at the discretion of the site investigator
- Upon resolution of dehydration at the discretion of the site investigator
- Upon resolution of symptomatic biliary sludge
- Upon resolution of symptomatic cholelithiasis
- Upon resolution of *C. difficile* infection
- If absolute neutrophil count (ANC) returns to normal range

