**Subjects can not be rechallenged with study drug under the following circumstances:**

- If the subject is diagnosed with invasive candidiasis
- If the subject is diagnosed with AIN or ATN
- If the subject is diagnosed with renal failure
- If the spot urine protein is greater than 1000 mg

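### Section 7.3 allows study drug to be resumed after any resolved catheter bloodstream infection, with no exception for Candida, although Section 8.1 bars rechallenge after invasive candidiasis

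*Combined protocol and SAP*

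**What the plan says.** **Catheter text.** Section 7.3, under Intravascular Related Infections, deals with bloodstream infection from the central line. It includes Candida species in its list of common organisms and calls for the catheter to come out if there is a fungemia. On therapy it says: "Treatment should be guided by the organism or organisms identified in the blood cultures". It closes with the restart rule: "Once the infection has resolved, the study drug may be resumed". No organism is excepted.

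**Drug text.** Section 8.1 lists the conditions that require suspension, among them: "If the subject is diagnosed with invasive candidiasis". Two lists follow. One opens "Subjects may be rechallenged with study drug under the following circumstances" and has entries for resolved *C. difficile* infection and colitis but none for any fungal infection. The other opens "Subjects can not be rechallenged with study drug under the following circumstances" and names invasive candidiasis again, without limiting it by source of infection or by resolution.

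**What counts as invasive candidiasis.** Section 7.1, Candidiasis, says: "Invasive candidiasis/sepsis involves more extensive monitoring of vital signs and serum white blood cell count". It continues: "Complete blood count with differential, blood culture, blood pressure, temperature should all be evaluated".

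**Related rules.** Section 8.2 (catheter complications) mentions fungemia only as a reason to remove the catheter. It describes drug suspension as temporary and has no bar on restarting. Section 5.4.3 leaves rechallenge to the site investigator once the event resolves, with prior notice to the Coordination Center.

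**The concern.** For a resolved Candida bloodstream infection from the line, the catheter text permits a restart that the drug text, on its natural reading, forbids. A site that handles the event as a catheter complication would read 7.3, 8.2 and 5.4.3, and none of these mentions the bar. Another site that starts from 8.1 would stop the drug for good.

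Section 7.1 links candidiasis to concurrent antibiotic use, and the active treatment is a long-term antibiotic given through a central line, so the bar has a clear safety purpose. At stake are the protection of a small number of subjects and uniform conduct across about 70 sites. Sample size, power and error control are not affected.

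**Working it through.** The plan gives no figure on this point, so the main check is a comparison of texts.

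**Step 1: does 7.3 cover Candida?** Yes. It names Candida species and fungemia. It separates organisms when deciding on catheter removal (*S. aureus*, fungemia, coagulase-negative staphylococcus, gram-negatives), but the restart sentence makes no such distinction.

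**Step 2: does the 8.1 bar cover Candida in the blood?** Most naturally, yes. Section 7.1 joins invasive candidiasis to sepsis and asks for blood culture. Its examples of invasive disease do not include candidemia, but they are introduced as examples, so the list is open.

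**Step 3: is resuming the same as rechallenge?** Section 5.4.2 suspends drug for a serious event. Restarting after a serious bloodstream infection is then a rechallenge under 5.4.3.

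**Step 4: what does each place tell a site to do?**

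| Place | Resolved Candida bloodstream infection |
|---|---|
| 7.3 Intravascular Related Infections | Drug may be resumed |
| 8.2 Catheter complications | Catheter removed for fungemia; suspension described as temporary; no bar |
| 5.4.3 Dosage Re-challenge | Investigator may rechallenge after resolution |
| 8.1 No-rechallenge list | Rechallenge barred |

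**Step 5: how often could it arise?** The inputs are 600 subjects, the average of 18 months on treatment in Section 6.3.4, and the rate in 7.3 ("catheter-related bloodstream infections was identified as 0.34 for every 1000 days of use").

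- Catheter-days: 18 months = 547.5 days; 600 × 547.5 = 328,500.
- Bloodstream infections, any organism, both arms: 328,500 × 0.34 / 1000 = 111.7, about 112 events.
- Candida share: not in the documents. Assumed 1–10%: 111.7 × 0.01 = 1.1 to 111.7 × 0.10 = 11.2 events.
- On ceftriaxone: about two thirds by allocation (40 of about 60 in Stage 1, 360 of 540 in Stage 3; 400/600). 1.1 × 2/3 = 0.7 to 11.2 × 2/3 = 7.5.
- Resolved and restarted: also not in the documents. If half were, 0.6–5.6 events in both arms, or about 0.4–3.7 on ceftriaxone.

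These are events, not subjects. The last three lines depend on the assumed shares.

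**The case against.** The strongest reply is that the two rules can be reconciled. The introduction to Section 7 sends events requiring discontinuation to Section 8, and Section 5.4.4 says that some conditions require permanent discontinuation for safety. A permission to resume can yield to a specific prohibition, and a site that obeys both simply does not restart. This stands: a reader might infer that the protocol compels opposite actions, and it does not. What remains is that the pointer is general. Section 8 has two tracks, and the one headed for catheter complications names fungemia without the bar.

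A second reply is that the tracks were meant to be separate. Section 8.1 is headed as related to ceftriaxone use, the word fungemia appears only in the catheter text, and the examples in 7.1 omit candidemia. A reader might therefore treat it as settled that 8.1 covers catheter-related candidemia. The documents support this only as the most natural reading. Equally, nothing in 8.1 exempts a catheter source.

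Third, there are safeguards: referral to an infectious disease specialist, notice to the Coordination Center before rechallenge, and Medical Monitor and DSMB review of serious event reports. They make an unnoticed restart less likely, but as written in the protocol none refers to the 8.1 list. Section 5.4 places dosage-change instructions in the Manual of Operations, and 7.1 sends sites to its management plans. The Manual was not available, so it cannot be said that sites have no exception to hand.

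A reader might also infer that 7.3 conflicts with 8.1 by letting drug continue during infection. That sentence concerns suspected infection, whereas 8.1 applies on diagnosis, so there is no conflict.

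**Conclusion.** The concern holds as a gap on a safety rule: followed as written, the 7.3 restart sentence can return drug to a subject whom 8.1 bars from rechallenge, and neither 8.2 nor 5.4.3 corrects it. The conclusion rests on candidemia being invasive candidiasis in the protocol's sense, which is likely but not stated, and on the protocol text alone, without the Manual of Operations.

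The frequency is low and cannot be derived from the documents. The figure of about 112 infections comes from the protocol's own inputs; the range of roughly 1–11 Candida events depends on an assumed share, and the number restarted would be smaller still. It would be wrong to read any of these as a forecast of harmed subjects. The change is worth making because it protects subjects at almost no cost.

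**What to change.** Three linked edits:

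1. In Section 7.3, extend the sentence "Once the infection has resolved, the study drug may be resumed" with: *except where Section 8.1 bars rechallenge (invasive candidiasis, including Candida bloodstream infection)*.
2. In Section 8.2, repeat the bar beside the entry that orders catheter removal for fungemia.
3. In Section 5.4.3, make the investigator's discretion subject to the no-rechallenge list in 8.1.

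Any related Manual of Operations text should be brought into line. The exception is workable because 7.3 already guides treatment by the blood culture result, so the organism is normally known before a restart is considered.

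The cost is a few clauses and slightly less time on drug for the few subjects affected. They stay in follow-up and in the intention-to-treat analysis, so no analysis changes.

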### **Catheter Thrombosis**

The formation of thrombin sheaths occurs in as high as 66% of central catheters. However, only 6% of these identified cases go on to develop and symptoms [133]. Typically, dysfunction in the ability to aspirate or infuse into the catheter is initially seen, and may lead to complete obstruction if not treated [135].

The patient is asymptomatic when thrombosis is confined to the catheter. The only signs may be the inability of the catheter to freely infuse or aspirate. Upper extremity edema may indicate a deep vein thrombosis and this should be ruled out, if present.

The catheter should not be removed, unless recommended by interventional radiology. If the catheter is removed, the study drug may be temporarily suspended or given peripherally.

### **Chest Wall Discomfort**

As with any surgical procedure, some chest wall discomfort from the placement of the catheter is to be expected. Discomfort or tenderness that exceeds the expected severity or time involved for healing should be investigated further.

### **Pneumothorax**

Pneumothorax is a problem that can develop while placing the catheter. It occurs at a rate of 0-3.3% when radiologically placed. Incidence of pneumothorax appears more frequent with the use of the subclavian vein and rare with the use of the jugular vein [131].

Placement of a tunneled catheter is followed by radiographic evaluation to rule out any pneumothorax, symptomatic or not. Intervention is determined by the degree of pneumothorax.

## **Pulmonary Embolus**

Catheter-related incidence of pulmonary embolus occurs in 12-36% of all cases of upper extremity deep vein thromboses related to catheter use [130]. The risk of air embolus has been assessed as between 0.6-0.8%, with most of these being small and asymptomatic. Serious adverse effects from air embolus are infrequent [131].

Pulmonary embolus is often difficult to recognize clinically, which contributes to its high mortality. Diagnostic symptoms may include anxiety, dyspnea, chest pain, tachycardia, diaphoresis and tachypnea.

In the event of a pulmonary embolus, the central catheter should be removed because of the higher incidence of the catheter causing additional emboli [181]. If the subject is clinically stable, the study drug can continue or it can be resumed via a peripheral line temporarily.

## **8. CRITERIA FOR INTERVENTION SUSPENSION, RECHALLENGE, OR PERMANENT DISCONTINUATION**

### **8.1 Intervention Suspension Related to Ceftriaxone Use**

**Study drug will be suspended under the following circumstances:**

(Please refer to the Manual of Operations for details regarding management of AEs)

- If the subject has *C. difficile* infection and is concurrently systemically ill with fever, leukocytosis or if the symptoms are refractory to treatment
- If the *C. difficile* infection results in pseudomembranous colitis
- If the subject is being treated for severe dehydration
- If the subject is symptomatic from biliary sludge
- If the subject is diagnosed with symptomatic cholelithiasis
- If the subject is diagnosed with invasive candidiasis
- If the subject is diagnosed with acute interstitial nephritis
- If the subject is diagnosed with acute tubular necrosis
- If the subject is diagnosed with renal failure
- If the serum creatinine doubles as compared to the screening visit value, the test will be repeated. If the value is confirmed (doubled as compared to screening visit value), study drug will be suspended while subject is evaluated.
- If the urinalysis is positive for Wright's or Hansel's stain as this is suggestive of eosinophiluria, or allergic interstitial nephritis
- If the spot urine protein is greater than 1000 mg. This is likely an indication of severe renal toxicity
- If the subject becomes oliguric, which is defined as urine output less than 500 mL/day. This can be an indication of severe renal toxicity
- If the Absolute Neutrophil Count (ANC) is less than 1.2 th/cmm

**Subjects may be rechallenged with study drug under the following circumstances:**

- Upon resolution of pseudomembranous colitis at the discretion of the site investigator
- Upon resolution of dehydration at the discretion of the site investigator
- Upon resolution of symptomatic biliary sludge
- Upon resolution of symptomatic cholelithiasis
- Upon resolution of *C. difficile* infection
- If absolute neutrophil count (ANC) returns to normal range

**Subjects can not be rechallenged with study drug under the following circumstances:**

- If the subject is diagnosed with invasive candidiasis
- If the subject is diagnosed with AIN or ATN
- If the subject is diagnosed with renal failure
- If the spot urine protein is greater than 1000 mg

**8.2 Intervention Suspension Due to Catheter Complications**

**Study drug will be suspended temporarily under the following circumstances:**

- If the subject is hemodynamically unstable
- If suspension is recommended by Infectious Disease
- If the catheter is unable to infuse
- If the catheter is accidentally removed or if its integrity is in question
- If the subject and family need further education to conform to the standards of safety and sterility

**The catheter will be removed under the following circumstances:**

- If there is a proven sepsis from *Staphylococcus aureus*, the presence of a fungemia or if the subject is hemodynamically unstable due to, or presumed to be due to, catheter sepsis.
- If the catheter is accidentally withdrawn to the point that it is no longer in a large vein which can sustain long standing intravenous therapy
- If the care provided by the subject and caregiver, in spite of attempts at re-education, does not meet the basic standards of safety and sterility
- If there is a demonstrated deep vein thrombosis
- If there is a high clinical probability of, or, demonstrated pulmonary embolus felt to be thrombosis related
- If removal is recommended by Infectious Disease or Interventional Radiology

**9. STATISTICAL CONSIDERATIONS**

**9.1 General Design, Data Analysis and Power**

The senior biostatistician at Massachusetts General Hospital will be primarily responsible for the biostatistical component of this study. The pharmacology consultant at Tufts University School of Medicine is primarily responsible for the pharmacokinetic analysis in STAGE 1.

### 9.1.1 STAGE 1 Pharmacokinetic Analysis and Sample Size

The primary purpose of the STAGE 1 study will be to determine if the 20th percentile of the trough level is significantly greater than 1µM. This would imply that at least 80% of the subjects would receive a minimum dose of 1µM. We intend to use a log-normal model for this calculation. Using a normal approximation, with 20 subjects, we would have an 80% chance of rejecting the null hypothesis that the 20th percentile of the trough level is 1µM or less at a two sided  $p = 0.05$  significance level if the true trough level was 1.44µM or more, based on a 50% coefficient of variation in trough levels. Based on a preliminary analysis of ceftriaxone in CSF [84], we were able to project the steady state trough levels by fitting the  $t_{\max}$ ,  $c_{\max}$ , and  $AUC_{0-\infty}$ , and half life given in Appendix 1 (Table 1) to a model where CSF ceftriaxone concentrations are assumed to be consistent with a one-compartment model, with first-order entry (rate constant:  $K_a$ ) and exit (rate constant:  $K_e$ ) from the CSF compartment. Based on that data the trough levels for a once a day dose would be 1.44 µM and for a twice a day dose would be 3.22 µM.

The secondary purpose of the Pharmacokinetic study is to determine the population pharmacokinetics of ceftriaxone in plasma and CSF. Knowledge of the distribution of the pharmacokinetic parameters will allow us to estimate the effect of a weekend drug holiday for the subjects, other alterations in the dosing schedule and the mean and standard deviation of the average exposure to the drug. Since this estimation may be difficult given data on trough levels and only one other time point, we are prepared to use three different estimation techniques. We plan to model CSF concentrations alone and jointly with plasma levels [182]. Ideally, a joint model will allow us to predict CSF levels using plasma levels. The three methods are NONMEM, which would be performed by our pharmacology consultants, who have experience using this program and the R function NLME [183] and PKBugs [184], which would be performed by our senior statistician. NONMEM and NLME both fit a random effects model to the data. The program PKBugs uses a Bayesian framework and should lead to more stable estimates because prior information from a full pharmacokinetic study will be utilized. The prior distribution of the parameters will be based on the data in Nau and colleagues [84]. In the final model we will consider covariates such as subject gender, height, weight and extent of disease.

**Plasma Pharmacokinetics.** Based on existing data, it is assumed that plasma kinetics of ceftriaxone are consistent with a two-compartment model. Accordingly, plasma concentrations are analyzed by derivative-free weighted nonlinear least-squares regression analysis (SAS PROC NLIN). The following equation is fitted to the data points:

$$C = [Q/V_1] [(k_{21}-\alpha) (1-e^{\alpha T}) (e^{-\alpha t})/\alpha(\alpha-\beta)] + [Q/V_1] [(k_{21}-\beta) (1-e^{\beta T}) (e^{-\beta t})/\beta(\beta-\alpha)]$$

with appropriate adjustment for the acquisition of data at steady-state in the course of multiple-dose treatment.

In this equation,  $C$  is the plasma ceftriaxone concentration and  $t$  is the time after the start of the infusion.  $T$  is an additional variable dependent on the infusion duration.  $T = t$  at all points in

time during the infusion; after the infusion is complete,  $T$  becomes fixed at a value equal to the duration of the infusion.  $Q$  is the zero-order ceftriaxone infusion rate, and  $V_1$  is the apparent volume of the central compartment. The exponents  $\alpha$  and  $\beta$ , having units of reciprocal time, are hybrid rate constants (derived from the parameters of the two compartment model) representing the apparent distribution and elimination phases of the plasma concentration curve, respectively.  $K_{21}$  is the apparent first-order rate constant of return from peripheral to central compartments. The fixed values in the analysis are  $Q$  and the infusion duration. The iterated variables are:  $V_1$ ,  $\alpha$ ,  $\beta$  and  $K_{21}$ . These are used to calculate the following: total volume of distribution using the area method ( $V_d$ ), apparent half-life of distribution and elimination, and total clearance [185].

**CSF Pharmacokinetics.** Initially we model CSF and plasma concentrations separately. The CSF parameters below will therefore have different values than the plasma parameters above. From the study by Nau, CSF ceftriaxone concentrations are assumed to be well approximated with a one-compartment model, with first-order entry (rate constant:  $K_a$ ) and exit (rate constant:  $K_e$ ) from the CSF compartment  $C = (D/V) * k_a * (\text{Exp}(-k_e * t) - \text{Exp}(-k_a * t)) / (k_a - k_e)$ . For population models, we would model  $V$ , and  $k_e$  as having a log normal between subject distribution. To obtain a preliminary estimate of the variability in our estimates of pharmacokinetic parameters and to determine the best time points for the second sample, we plan to conduct simulation studies. From Nau et al. we estimate  $k_a = 0.116/\text{hr}$ ,  $k_e = 0.04/\text{hr}$ .  $(1/V) = 0.00044305/\text{L}$ . We would generate 100 data sets of 20 subjects on once a day 2 gram dosing and 20 subjects on twice a day 2 gram dosing. Population pharmacokinetics would be generated from each data set. The between subject coefficient's of variation, and the measurement error would be assumed to be similar to other studies. We would perform simulations for the combined doses and for each dose separately with various parameter choices. We conducted a pilot simulation to see if the proposed model was estimable. We generated data based on parameters estimated from the Nau ( $k_a = 0.116/\text{hr}$ ,  $k_e = 0.04/\text{hr}$ .  $(1/V) = 0.00044305/\text{L}$ ) and picked the time points at random during the first 12 hours. We found that all of the parameters,  $V$ ,  $k_e$ ,  $k_a$ , the population standard deviations and the error variance were estimable. The value of  $t_{\max}$  calculated from these parameters had a standard error of 2 hours and the  $c_{\max}$  had a standard error of 0.06. We conclude that our analysis plan is reasonable and will estimate the parameters with enough precision for our purposes.

**Joint Pharmacokinetic Model.** Our initial model would be to use the plasma model described above and assume that there are two additional parameters representing diffusion from the plasma into the CSF and from the CSF back into the plasma.

